#### **12.1.2 Systemic adverse events**

Temperature will be measured by the axillary route prior to immunization and 30 minutes after the immunization by study personnel and graded according to the DAIDS Table for Clinical and Lab Criteria for Definitions. Participants will be given thermometers to record their temperature in the diary card on the evening of immunization, and daily thereafter for 7 days, and if still raised, they will be advised to continue to monitor their temperature daily until it returns to normal. The temperature observed by the clinical team will be recorded in the case record forms for visits. In case of grade 3 and 4 fever, malaise, chills/rigors and headache, and where indicated, additional tests to exclude other common causes of fever like malaria will be performed.

Chills, headache, nausea, malaise, myalgia, and arthralgia will be graded by the participants according to mild, moderate or severe impression and recorded in the diary card on the evening following immunization and daily for 7 days, or until resolution of symptoms whichever is longer. At the next study clinic visit diary entries will be reviewed and discussed by the medical officer with the participants and events will be transferred into the case report form according to the DAIDS Table for Clinical and Lab Criteria for Definitions. Data entry in the CRF will take precedence over diary card entries in the analysis. Study personnel will verify all grade 3 or 4 events.

#### **12.1.3 Other adverse events**

These will be recorded as reported following an open question to volunteers, with the dates of commencement and resolution, the outcome at the end of the study, required treatment, relationship to the study agent and potential effects on the vaccination schedule. They will be graded according to the general principles outlined in the DAIDS Table for Clinical and Lab Criteria for Definitions. Social harm will also be recorded as an adverse event, graded according to the general guidelines (which include denial of health and life insurance,

employment, immigration and marriage relationships). All grade 3 or 4 events will be verified by study personnel.

#### **12.1.4 Routine laboratory parameters for safety assessments**

The following safety assessments will be undertaken at appropriate laboratories at MUHAS and MMRP according to standard operating procedures. All lab values will be interpreted according to established MMRP and MUHAS local reference ranges. Lab results requiring AE reporting after enrolment will be graded according to the DAIDS Table for Clinical and Lab Criteria for Definitions (*see Appendix 9*). In order to harmonize with local reference ranges, the cut-off for Grade I lab toxicity reporting have been modified for neutrophils from  $\leq 1.300$  cells/ $\mu$ l (DAIDS) to  $\leq 1.100$  cells/ $\mu$ l (local values).

##### Hematology

Hemoglobin; white blood cell count, total and differential counts, specifically granulocytes and lymphocytes; platelet count and red blood cell counts.

##### Clinical chemistry

Liver function tests (ALT, bilirubin total and direct), serum creatinine and blood glucose. A Troponin I test will be performed 2 weeks after each MVA vaccination.

##### Immunology

Determination of CD4 counts and percentage only at the enrolment visit.

##### Serology

Syphilis (VDRL, and when necessary TPHA) and screening for HBsAg during screening. Tests might be repeated during the study if clinically indicated.

##### Urinalysis

Urine dipsticks will be performed during screening and at each vaccination day by clinical nursing staff and recorded as normal/abnormal. If abnormal results are seen ( $\geq +1$ ) urine specimen will be send to the clinical lab for microscopic analysis and validation. Results will be graded by a study Physician as normal, abnormal/clinically insignificant and abnormal/clinically significant.

##### Pregnancy test

Pregnancy test will be performed by study nurses at the clinic or at the study lab from urine during screening, at each vaccination day with results available before vaccine administration and at the long term follow-up visits 17 (week 58) and 18 (week 70)."

##### ECG

ECG will be done during screening/before enrolment as a baseline assessment to exclude volunteers with significant ECG findings. Significant ECG findings leading to exclusion are defined as "Abnormality in ECG that could indicate risk or make interpretation of vaccine effects difficult according to the study operating procedures." According to this definition volunteers will be excluded who have:

1. Evidence in the ECG for cardiologic disease
2. Variations in the ECG which might not be clinical significant but will complicate later interpretation for post vaccination ECG results.

ECG's will be interpreted by competent study physicians and be graded as **normal**, **abnormal/clinically insignificant** and **abnormal/clinically significant**. Any abnormal finding

will be commented in the case report form (**CRF 9-III**). All ECG's will be sent prior to enrolment to a cardiologist panel for review and approval via email. The final verdict on the ECG with regards to enrolling or not enrolling the volunteer into the study will be provided by the Chairperson of the panel. The ECG panel will consist of:

**[name]**

[[contact]](mailto:[contact])

ECG will be repeated 2 weeks post MVA/Placebo vaccinations or at anytime whenever a volunteer comes with symptoms and signs suggestive of peri-myocarditis. Results will be interpreted and compared to baseline ECG results by competent study physicians and send to the cardiologist panel for review and approval. Post vaccination ECG will be graded as **normal**, **abnormal/clinically insignificant** and **abnormal/clinically significant**. Post vaccination ECG findings will be graded as **no changes**, **changes/not significant** and **changes/significant** as compared to baseline results. Any abnormal finding and changes will be commented in the case report form (**CRF 9-III**).

All grade 3 or 4 adverse events or serious events and/or those that necessitate a physician's visit or are treated with a prescribed medication will be evaluated. The volunteer will be followed carefully until the condition is resolved and/or the cause is identified. Any medication or other therapeutic measure taken to relieve symptoms of the medical problem must be recorded on the appropriate case report form page(s) (**CRF 4-I**) in addition to the outcome of the adverse event (**CRF 6-1**). Where a diagnosis is possible, it is preferable to report this rather than a series of terms relating to the diagnosis. When reporting a syndrome, the associated signs and symptoms will be parenthetically indicated following the syndrome rather than as separate events

#### **12.1.5 Following adverse event**

Other assessments (e.g. extended clinical chemistry, malaria microscopy, stool analysis, urine culture, TB culture) may be performed as clinically indicated at the sites due to an adverse event. There is the possibility to ship blood samples for specific investigation to specialized laboratories in Europe for further diagnosis.

### **12.2 Immunogenicity assessment**

#### **12.2.1 Antibody responses**

Antibodies to HIV proteins covering the vaccines will be assessed using ELISA. Following completion of the study, neutralizing antibodies to HIV subtypes A, C and D will be performed at SMI if binding antibodies are detected.

Serum samples at different time points will be collected as per specimen schedule and will be stored until the time for the assays at the end of the study. In vivo antibody neutralization will be used for testing. At this point in time, it is not known which time point sample is going to induce broadly neutralizing antibodies or not. Therefore, testing will be performed on the last serum sample collected 2 weeks post vaccination and other earlier time point samples should the last sample testing show any interesting results

The specific assessment of HIV-1 specific antibody responses will thus include:

- Serum binding antibody determination by ELISA and Western blot assay

- Serum neutralization antibody assay including cross clade reactivity (against HIV-1 subtypes A, C and D which are prevalent in Tanzania)

### 12.2.2 Cellular responses

The following HIV-1 specific cellular immune responses will be determined:

- CD8 and CD4 T cell responses
  - IFN- $\gamma$  ELISPOT using fresh PBMC including determination of cross clade responses, using pools of overlapping peptides representing env, gag and pol proteins
  - IFN-  $\gamma$ /IL-2 Intracellular cytokine staining (ICS) using fresh PBMC and conducted against the same peptide pools as in the ELISPOT and testing both for CD8 and CD4 T cell responses
  - Multicolor ICS staining for measuring polyfunctional responses using cryo-preserved PBMC, including cytokines/chemokines and CD107 (for assessment of degranulation activity) and testing for both CD8 and CD4 T cell responses
- Mainly CD4 T cell responses  
Lymphocyte proliferation assay (LPA) to the immunizing antigens using fresh PBMC and a standard  $^3\text{H}$ -thymidine uptake assay and /or a flow cytometry-based assay (CFSE staining or FASCIA). A comparative evaluation of lymphocyte proliferation assays for measuring HIV vaccine-induced immune responses will be performed before the start of the TaMoVac trial.
- Optional assays
  - Viral inhibition assay
  - Cytotoxic T lymphocytes (CTL) by chromium release assay

The primary immunogenicity endpoint will be measured by a standard IFN- $\gamma$  ELISPOT assay using fresh PBMC. ELISPOT responses are considered positive if the numbers of spot-forming cells (SFC) are at least four times the background (RPMI medium only) and > 55 SFC per million PBMC (Merck definition).

Quality control and exchange of specimens with international laboratories will be performed.

### 12.2.3 Storage of Cell pellets for HLA testing

Lymphocyte cell pellets will be stored at the MUHAS department of Microbiology/Immunology and at the MMRP Immunological Lab for later HLA typing that will be performed by molecular methods at a laboratory to be identified later.

## 12.3 Other assessments

### 12.3.1 HIV testing

Samples will be tested at MUHAS Department of Microbiology/Immunology and at MMRP laboratories using HIV antigen/antibody ELISA. Positive results will be confirmed by a duplicated second ELISA and after confirmation with a HIV PCR. In the case of discordant results a duplicated second ELISA and if needed a Western Blot analysis and HIV PCR will be used (**see Appendix 7**).

### 12.3.2 Antibodies against Vaccinia

Serum samples will be stored at MUHAS, Department of Microbiology/Immunology and MMRP for later testing.

## 13 CONCOMITANT MEDICATION

Volunteers/participants will be asked about medication taken at each visit. All medication including other vaccinations (e.g. tetanus toxoid) or herbal/traditional remedies will be recorded in the case record form (**CRF 4-I**). Documentation should include the generic name of the drug, indication for use, dose and route of administration, frequency, start and stop dates. For medication available over the counter or other sources, the maximum information available on questioning the volunteer will be recorded. For combination medication all generic drug names included will be named into one entry (e.g. Coartem® = Artemether + Lumefantrine). For herbal or traditional remedies as much information as possible will be sought about the content, the indication or the indigenous name.

## 14 ADVERSE EVENTS

### 14.1 Definitions and Classification

An adverse event (AE) is any untoward medical occurrence in a patient or clinical investigation subject administered a pharmaceutical product and which does not necessarily have a causal relationship with this treatment. An AE can therefore be any unfavorable and unintended sign (including an abnormal laboratory finding), symptom, or disease temporally associated with the use of a medicinal (investigational) product, whether or not related to the medicinal (investigational) product (ICH E6). An adverse event in this study is any adverse experience occurring during the course of the study starting **after vaccination** and will be documented in the adverse report form (CRF 6-I). During the screening period any previous, current or ongoing conditions will be documented in the previous condition case report form (CRF 4-II). Adverse reaction as defined in the vaccine/reaction form (CRF 10-I) during the 7 days post vaccination will not be again recorded in the AE case report form unless one of the symptoms can be clearly associated with another diagnosis (e.g. fever post vaccination with the diagnosis of confirmed malaria). Criteria for grading clinical and laboratory events are listed in the DAIDS Table for Clinical and Lab Criteria for Definitions (**see Appendix 9**).

The severity of events reported on the adverse event form will be determined by the investigator, based on the Toxicity Grading Scale or if the event is not listed the event will be graded following these guidelines:

- Mild (Grade 1): Transient or mild symptoms; no limitation in activity; no intervention required. Symptoms causing no or minimal interference with usual social and functional activities
- Moderate (Grade 2): Symptoms causing greater than minimal interference with usual social and functional activities. No or minimal intervention required. It is uncomfortable or an embarrassment.
- Severe (Grade 3): Symptoms causing inability to perform usual social and functional activities. Medical intervention often required.
- Life-threatening (Grade 4): Symptoms causing inability to perform basic self-care functions OR Medical or operative intervention indicated to prevent permanent impairment, persistent disability, or death.

The relationship of adverse events to study product will be classified as:

|                              |                                                                                                                                                                                                                                                                                                                                    |
|------------------------------|------------------------------------------------------------------------------------------------------------------------------------------------------------------------------------------------------------------------------------------------------------------------------------------------------------------------------------|
| Not related:          | Adverse events felt to be due to extraneous causes that neither follows a known pattern of response nor a reasonable temporal relationship to study product.                                                                                                                                                                       |
| Probably not related: | Adverse events that are unlikely to be related to product but which follow a reasonable temporal relationship, such that this cannot be completely excluded or events that could be associated with product but which are unrelated in time.                                                                                       |
| Possibly related:     | Adverse events that may be due to extraneous causes but which follow a known pattern of response and/or a reasonable temporal relationship to study product.                                                                                                                                                                       |
| Probably related:     | Adverse events that cannot be explained by extraneous causes; which follow a known pattern of response and/or a reasonable temporal relationship; which disappear or decrease on cessation of study product and reappear on re-challenge.                                                                                          |
| Definitely related:   | Adverse events that have a definite relationship to the study agent (e.g. anaphylactic reaction after vaccination) without any other explained causes; which follow a known pattern of response and/or a reasonable temporal relationship; which disappear or decrease on cessation of study product and reappear on re-challenge. |

A severe adverse event is any **graded 3 or 4** by criteria in DAIDS Toxicity Table (*Appendix 7*). Some, but not all grade 3 and 4 adverse events will be “serious” by ICH GCP criteria below.

#### **14.2 Serious Adverse Events (SAEs)**

An adverse event is considered to be a “serious adverse event” by ICH Good Clinical Practice (ICH E6 and E2A) criteria if it results in the following:

1. Death,
2. A threat to life (any grade 4 event)
3. Requires in-patient hospitalization or prolongs existing hospitalization (hospitalization for elective treatment of a pre-existing condition is not included),
4. Results in persistent or significant disability or incapacity,
5. Is a congenital anomaly (i.e. the outcome of pregnancy involving a volunteer),
6. Is any other important medical condition\*.

\*Examples of conditions regarded as “any other important medical condition” include allergic bronchospasm requiring intensive emergency treatment, seizures or blood dyscrasias, which did not result in hospitalization or development of drug dependency.

Note that grade 4 lab abnormalities are not serious adverse events, unless they are related to a clinically event matching the SAE definition.

***Any HIV infection occurring throughout the study period will be defined as a Grade 4 Serious Adverse Event and has to be reported to the study monitor and DSMB accordingly.***

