**8.15 Study visit 15 – Follow up**  
**(Study week 48; 14 days after V14 +/- 3 days)**

This is the first follow up visit two weeks post 2nd MVA/Placebo vaccination. It is essentially a safety assessment visit and will be conducted as described for study visit 4. Blood draw (including Troponin I test when available) and filling of forms will be done according to the visit schedule. In addition a post vaccination ECG will be performed and results will be interpreted and compared to previous ECG as described for Study Visit 12. The participant will then be compensated and assigned to his next scheduled visit.

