#### **14.3 Reporting of adverse events**

Adverse and serious adverse events should be recorded on the appropriate case record form (**CRF 6-I**). Any grade 3 or 4 adverse event or any event resulting in discontinuation of the

vaccination schedule should be reported within 2 working days after site awareness to the study monitor, sponsor, TCC, WRAIR and DSMB. The TCC, WRAIR and DSMB will review and make the appropriate recommendations to the monitor, who will transmit these to the sponsor for a decision on the continuation of the study. The decision whether to continue, pause or discontinue the study will be submitted to the monitor, Steering committee, TCC, the local IRB, NIMR and TFDA for further review and action

Serious adverse events should be reported to the monitor and DSMB the same day on an expedited reporting level at the same working day that the Clinical Investigator becomes aware of the event when the following criteria are fulfilled:

1. Result in death regardless of relationship to study agent.
2. Congenital anomalies, birth defects, or fetal losses regardless of relationship to study agent.
3. Result in persistent or significant disabilities or incapacities regardless of relationship to study agent.
4. Any suspected adverse drug reaction, i.e., definitely, probably, possibly, and probably not related to a study agent that requires or prolongs existing hospitalization, or requires intervention to prevent significant/permanent disability or death.
5. Any life threatening (including all Grade 4 adverse events) suspected adverse drug reactions, i.e., definitely, probably, possibly, and probably not related to a study agent.

“Life threatening” refers to an adverse event that at occurrence represents an immediate risk of death to the subject. An experience which may have caused death had it occurred in a more severe form is not considered life threatening. Similarly, a hospital admission for an elective procedure is not considered a Serious Adverse Event.

In addition to the reporting requirements described above, sites should report any of the following adverse events on an expedited basis:

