## 16.2 Criteria for pausing the study

1. The study monitor will closely monitor and analyze study data as it becomes available and will make determinations regarding the presence and severity of the adverse events and keep the sponsor informed.
2. Any grade 3 systemic event that has been judged to be definitely related to the vaccination (following exclusion of other unrelated common causes) or if one volunteer experiences grade 4 SAE assessed as possibly related to the vaccination. During the pause the DSMB will be consulted with the facts on the case, and a review of the event in a broader context will be undertaken. Their verdict will then be conveyed to the steering committee and the sponsor for review and decision on what to do next.
3. If any AE report raises concern that the study may cause significant harm to the participants following a safety board consensus decision (**See section 14.3 study monitor, sponsor, TCC, WRAIR and DSMB**).

The study injections and enrolments would resume only after review of the adverse events by the DSMB and a decision by the TCC and steering committee including the Chairman resulting in a recommendation to the sponsor to permit further study injections and study enrolments. These decisions will be cleared by the local IRBs, NIMR and TFDA. Safety data and changes in study status will be submitted to the ethics committee.

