| PARAMETER                                   | GRADE 1
MILD                         | GRADE 2
MODERATE                     | GRADE 3
SEVERE                                        | GRADE 4
POTENTIALLY
LIFE-THREATENING                                                                           |
| Adult and Pediatric
≥ 7 days     | 10.6 – 11.5 mg/dL
2.65 – 2.88 mmol/L | 11.6 – 12.5 mg/dL
2.89 – 3.13 mmol/L | 12.6 – 13.5 mg/dL
3.14 – 3.38 mmol/L                  | > 13.5 mg/dL
> 3.38 mmol/L                                                                                        |
| Infant*†, < 7 days     | 11.5 – 12.4 mg/dL
2.88 – 3.10 mmol/L | 12.5 – 12.9 mg/dL
3.11 – 3.23 mmol/L | 13.0 – 13.5 mg/dL
3.245 – 3.38 mmol/L                 | > 13.5 mg/dL
> 3.38 mmol/L                                                                                        |
| Calcium, serum, low (corrected for albumin) |                                         |                                         |                                                          |                                                                                                                      |
| Adult and Pediatric
≥ 7 days     | 7.8 – 8.4 mg/dL
1.95 – 2.10 mmol/L   | 7.0 – 7.7 mg/dL
1.75 – 1.94 mmol/L   | 6.1 – 6.9 mg/dL
1.53 – 1.74 mmol/L                    | < 6.1 mg/dL
< 1.53 mmol/L                                                                                         |
| Infant*†, < 7 days     | 6.5 – 7.5 mg/dL
1.63 – 1.88 mmol/L   | 6.0 – 6.4 mg/dL
1.50 – 1.62 mmol/L   | 5.50 – 5.90 mg/dL
1.38 – 1.51 mmol/L                  | < 5.50 mg/dL
< 1.38 mmol/L                                                                                        |
| Cardiac troponin I (cTnI)                   | NA                                      | NA                                      | NA                                                       | Levels consistent with myocardial infarction or unstable angina as defined by the manufacturer                       |
| Cardiac troponin T (cTnT)                   | NA                                      | NA                                      | NA                                                       | ≥ 0.20 ng/mL
OR
Levels consistent with myocardial infarction or unstable angina as defined by the manufacturer |

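### The protocol does not settle whether an isolated Grade 4 troponin I rise after MVA meets the automatic pause trigger, and it requires the second troponin test in some places but makes it conditional in another

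*Protocol*

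**What the plan says.** Seriousness (section 14.2): item 2 of the SAE list reads "A threat to life (any grade 4 event", with no exception for laboratory values. Below the list stands: "Note that grade 4 lab abnormalities are not serious adverse events", with the proviso that they do count when tied to a clinical event that itself qualifies as an SAE.

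Reporting (section 14.3): item 5 of the same-day list covers "Any life threatening (including all Grade 4 adverse events) suspected adverse drug reactions", again with no laboratory exception. Later in 14.3, in the bullet on events after the expedited reporting period, sites are told not to report Grade 4 laboratory values that lack a life-threatening clinical event.

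Pausing (section 16.2): item 2 is the automatic rule. It is met by a Grade 3 systemic event judged definitely related, or by one volunteer with a "grade 4 SAE assessed as possibly related to the vaccination". Item 3 allows a pause on any AE report that raises concern of significant harm, by safety board consensus.

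Grading (Appendix 9): the troponin I row has no entry for Grades 1 to 3. Grade 4 is "Levels consistent with myocardial infarction or unstable angina as defined by the manufacturer".

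Timing: under Clinical chemistry, section 12.1.4 states "A Troponin I test will be performed 2 weeks after each MVA vaccination". Section 8.12 includes the test at visit 12 without condition, and Appendix 3 schedules it at V12 and V15. Section 8.15, for visit 15, has "including Troponin I test when available".

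**The concern.** Section 4.3 explains that MVA recipients get extra cardiac monitoring because of complications seen with unattenuated vaccinia vaccine. Troponin I is the only cardiac laboratory test planned after MVA. For a rise at the level in the troponin row, two statements in 14.2 give opposite answers on seriousness, and 16.2(2) uses seriousness as its switch. Two sites could apply the text in good faith to the same result, and one would pause while the other would not. The pause rule is a single-case rule, so no later accumulation of data corrects a first case that was handled differently.

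The wording in 8.15 raises a second, smaller matter. If availability decides whether the test is done at visit 15, the cardiac laboratory data after the second boost may be incomplete, and incomplete to a different degree at each site.

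**Working it through.** No sample size, error rate or event count enters, and the plan states no figure to reproduce. The check applies each rule to one case: a troponin I value at the Appendix 9 Grade 4 level, after an MVA injection, assessed as possibly related, with no clinical event.

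1. **Grade.** By the troponin I row: Grade 4, the only level defined there.
2. **Serious, by 14.2 item 2?** Yes.
3. **Serious, by the 14.2 note?** No, because there is no qualifying clinical event.
4. **Same-day report, by 14.3 item 5?** Yes if the words on Grade 4 events are taken as they stand. The later instruction against reporting Grade 4 laboratory values points the other way, but it sits in the bullet on late events.
5. **16.2(2), Grade 4 limb?** Met if step 2 governs; not met if step 3 governs.
6. **16.2(2), Grade 3 limb?** Not met. The troponin row has no Grade 3, and the limb requires a definite relation.
7. **16.2(3)?** Can be met whatever the grade or seriousness, but needs a consensus decision.
8. **14.3, first paragraph?** Applies. Any Grade 3 or 4 AE is reported within 2 working days to the monitor, sponsor, TCC, WRAIR and DSMB, and a decision on continuing the trial follows.
9. **19.2.1?** The TCC may suspend the trial for any reason.
10. **19.5?** Not met by one case; three or more volunteers are needed.

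Steps 2, 3 and 5 show that the answer under the automatic trigger turns on which sentence of 14.2 is followed. Steps 7 to 9 show what remains on the note's reading.

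These remaining routes differ from 16.2(2) in timing. Under 16.2(2) the pause comes first and the DSMB is consulted while it lasts. Under 14.3 the site has 2 working days to report, and section 19.3 gives the DSMB 7 days to recommend. No text requires injections to stop in that interval.

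Appendix 9 adds a further ambiguity. Its cardiac ischaemia and infarction row places test results pointing to ischaemia at Grade 3. If a troponin result were graded there, the Grade 3 limb of 16.2(2) would apply, and a possibly related case would still not meet it.

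For test timing, 12.1.4, 8.12 and Appendix 3 set no condition at either visit, while 8.15 sets one at V15. These cannot all hold.

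**The case against.** The best answer is that 14.2 states a rule and then an exception. The note follows the list directly and carries its own proviso, and 14.1 has already said that not every Grade 3 or 4 event will be serious. Item 5 of 14.3 sits under a heading sentence about serious events and concerns life-threatening reactions, which the next paragraph defines by immediate risk of death. This reading is reasonable. It does not remove the point: it means that an isolated troponin I rise does not meet the Grade 4 limb of 16.2(2), and nothing in the protocol shows that this was intended.

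A reader might infer that such a rise lies outside the pause rule altogether. The documents do not support that, because 16.2(3), the 14.3 review of every Grade 3 or 4 AE and the TCC's power to suspend all remain. A reader might also infer that no abnormal troponin result can be graded 1 to 3. That is true of the troponin row only, given the ischaemia row. Nor would it be fair to read the pause trigger as excluding probable or definite relation; possibly related is naturally a floor.

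Two further points for the plan stand. An ECG is done at the same two visits and goes to a cardiologist panel, so troponin is not the only cardiac check. And section 4.3 reports no cardiac toxicity with MVA in ongoing studies.

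**Conclusion.** The concern holds in limited form. As written, the protocol does not determine whether an isolated, possibly related Grade 4 troponin I rise triggers the automatic pause in 16.2(2). On the note's reading it does not, and a pause then depends on discretionary decisions during which injections may continue. Separately, 8.15 contradicts 12.1.4 and Appendix 3 on whether the V15 test is mandatory.

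The effect is confined to one single-case safety trigger and one planned test at one of its two visits. It cannot be expressed as a number of affected events: the documents give no expected rate of troponin elevation, and counting scheduled tests would not supply one. The conclusion assumes that the value is graded on the troponin row and that no qualifying clinical event accompanies it. If either fails, other rows of Appendix 9 or the proviso in the note apply.

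**What to change.** Reconcile 14.2 item 2, the 14.2 note, 14.3 item 5, 16.2(2) and the cardiac rows of Appendix 9, so that one statement decides whether an isolated Grade 4 laboratory value, troponin I in particular, is an SAE and whether it counts for 16.2(2). State which Appendix 9 row governs a troponin result. Reconcile 8.15 with 12.1.4 and Appendix 3 on whether the V15 test is conditional. The clinical content of each rule is for the sponsor and DSMB to decide; the need here is that both sites read the same rule.

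The cost is a short text amendment with the usual approvals. It adds no visit, sample or procedure, since Appendix 3 already schedules troponin I from the biochemistry tube at V12 and V15.
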